## Methods

### Participants

This cross-sectional study will enroll a total of 100 participants, including 50 individuals diagnosed with plantar heel pain, along with 2 control groups. The first control group will consist of 25 individuals with insertional Achilles tendinopathy, for whom targeted myofascial treatments are not considered first-line interventions [23]. The second control group will include 25 pain-free individuals with a similar age, BMI, and sex distribution as the plantar heel pain and insertional Achilles tendinopathy groups. To ensure balanced representation, enrollment will be structured so that neither sex comprises more than 60% of each group. Eligibility and group assignment will be based on the inclusion and exclusion criteria outlined in Textbox 1. Screening for study eligibility will occur in three phases: (1) an online screening form, (2) a video visit with a physical therapist, and (3) an in-person clinical examination by a physical therapist. Individuals who provide informed consent and meet all criteria will be enrolled in this study.

Eligibility criteria.

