**Inclusion criteria**
For the plantar heel pain and insertional Achilles tendinopathy group:Clinical diagnosis of plantar heel pain [5] or insertional Achilles tendinopathy [23].Duration of pain ≥3 months.Severity of pain ≥3/10.

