**Exclusion criteria**
For all groups:Age <18 years.History of invasive procedures to the foot or ankle on the side of interest.History of lower extremity injections, dry needling, extracorporeal pulse activation treatment, or extracorporeal shockwave therapy within the past 3 months on the side of interest.Contraindications for MRI (eg, non–magnetic resonance–compatible implanted devices, claustrophobia, inability to remain still comfortably for 1 hour in a supine position [24])Clinically unstable medical or psychiatric issues.Comorbidities associated with changes in musculoskeletal imaging, including rheumatologic and inflammatory conditions that directly impact the musculoskeletal system (eg, rheumatoid arthritis, spondyloarthropathy, and gout), osteoarthritis of the foot or ankle, diabetes, neuromuscular diseases (eg, Charcot-Marie-Tooth [CMT] disease), familial hypercholesterolemia, history of foot or ankle fracture, neoplasms involving the foot, plantar fibromatosis, or recent (within the past 1 year) infection of the foot or ankle (eg, infectious fasciitis and calcaneal osteomyelitis).For the plantar heel pain and insertional Achilles tendinopathy group:Other sources of heel pain (eg, tarsal tunnel syndrome, peripheral neuropathy, lumbar radiculopathy, calcaneal stress fracture, fibromyalgia, Morton’s neuroma, or Baxter neuropathy).Additional exclusion criteria for insertional Achilles tendinopathy group: co-occurring plantar heel pain and Achilles tendinopathy.For the pain-free control group:Persistent or recurrent leg pain in the past 6 months.

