**Psychological factors**									
	PCS-6^f^		A short form of the Pain Catastrophizing Scale that measures catastrophic thinking about pain. It consists of 6 items across 3 subscales—2 items each for “rumination,” “helplessness,” and “magnification”—each scored from 0 to 4, yielding a total score of 0-24, with higher scores indicating greater catastrophic thinking [34,35].					Internal consistency: Cronbach α=0.88 Correlation with the full 13-item PCS: r=0.94 in individuals with chronic pain conditions	
	TSK-11^g^					Measures fear of movement using 11 items from 1 (“strongly disagree”) to 4 (“strongly agree”), yielding a total score of 11-44. Scores <22 indicate minimal fear, 23-28 low fear, 29-35 moderate fear, and ≥36 high fear [36,37].		Convergent validity: association with pain catastrophizing, severity of expected pain with movement, and willingness to complete tendon loading exercises in individuals with Achilles tendinopathy Test-retest reliability: ICC=0.81 (in individuals with back pain)	
	PHQ-2^h^		Screens for depression over the past 2 weeks using 2 items scored from 0 (“not at all”) to 3 (“nearly every day”), yielding a total range of 0-6. Scores of 0-2 suggest minimal or no depression, while scores ≥3 indicate possible depression requiring further evaluation [36].					Sensitivity: 83% Specificity: 92%	
	PROMIS^b^ Sleep Disturbance					Evaluates sleep quality and disturbances across 8 items, each scored from 1 (“not at all”) to 5 (“very much”), yielding raw scores of 8-40. Scores are converted to T-scores (mean 50, SD 10), ranging approximately from 20 to >80. T-scores of 55-60 indicate mild sleep disturbance, 60-70 suggest moderate disturbance, and >70 reflect severe sleep disturbance [37,38].		Internal consistency: Cronbach α=0.96 Convergent validity with the Pittsburgh Sleep Quality Index: r=0.85 Test-retest reliability: ICC=0.62-0.71 (in fibromyalgia populations)	

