	PROMIS^b^ Self-Efficacy for Managing Symptoms 8a			Assess the subject’s level of confidence in managing their symptoms in different settings (home, public place, and an unfamiliar place) and in keeping their symptoms from interfering with work, sleep, relationships, or recreational activities. Each item scored from 1 (“not at all confident”) to 5 (“very confident”), yielding raw scores from 8 to 40. Converted T-scores below 30 suggest very low, 30-40 low, 40-60 average, 60-70 high, and 70-80 reflect very high self-efficacy [39].					Internal consistency: Cronbach α=0.92 Correlations with Chronic Pain Self-Efficacy Scale: r=0.74 (in patients with chronic conditions)
	GAD-2^i^			Screens for generalized anxiety disorder by asking about the frequency of feeling nervous and unable to control worrying over the past 2 weeks. It uses 2 items, each scored from 0 (“not at all”) to 3 (“nearly every day”), totaling 0 to 6. Scores of 0 to 2 indicate minimal or no anxiety, while scores of 3 or higher suggest possible anxiety requiring further assessment [40].					Sensitivity: 76% Specificity: 81% Internal consistency: Cronbach α=0.89

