In an exploratory aim, composite biosignatures will be developed from imaging biomarkers, patient demographics, and psychological factors. Traditional statistical and machine learning techniques will be used. Logistic regression models, fit with the method of general estimating equations, will be used specifically to test for interactions between imaging biomarkers and sex. Composite models will be built from the full set of predictors using stepwise variable selection as well as the machine learning methods of Lasso, gradient boosting, and random forests. The latter 2 methods have the distinction of performing automated encoding of nonlinear and interaction effects. ROC AUC will be estimated as the measure of diagnostic performance for each model, as described for the primary aim. In addition, variable importance will be reported to quantify the relative contributions of predictor variables, and partial dependence plots will be constructed to show the functional forms of their effects.

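### Variable importance read as relative contribution over all 100 participants can credit pain-referenced psychological scores with a signal that comes only from recruiting pain-free controls

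*Protocol article*

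**What the plan says.** Under Statistical Analysis, Data Analysis, the article states that "composite biosignatures will be developed from imaging biomarkers, patient demographics, and psychological factors". Model performance is the ROC AUC as in the primary aim, where the outcome is tissue with or without myofascial pain, pooled over five muscles. In addition, "variable importance will be reported to quantify the relative contributions of predictor variables", and partial dependence plots show the form of each effect. The section names no restriction to the pain groups, no group term and no caveat about the recruited mix.

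Eligibility sets pain status. The two foot-pain groups need "Severity of pain ≥3/10" for at least 3 months; pain-free controls are excluded for "Persistent or recurrent leg pain in the past 6 months". The Participants section asks for "25 pain-free individuals with a similar age, BMI, and sex distribution as the plantar heel pain and insertional Achilles tendinopathy groups", and for enrollment in which "neither sex comprises more than 60% of each group".

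Table 1 lists six psychological measures. PCS-6 "measures catastrophic thinking about pain"; the PROMIS self-efficacy form asks about the "level of confidence in managing their symptoms in different settings". TSK-11 covers fear of movement. PHQ-2, GAD-2 and PROMIS Sleep Disturbance are not described in terms of pain.

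**The concern.** A score about pain or about managing symptoms is put to 25 people chosen for having no persistent or recurrent leg pain. It is likely to differ between them and the 75 with foot pain for that reason alone. If trigger-point tissue is also less common in the pain-free group, the score predicts trigger points in the pooled sample simply by marking who has pain. A model cannot tell this apart from a real link between psychology and myofascial tissue, and the importance ranking would show it as a contribution.

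The abstract, the Principal Findings paragraph and the Conclusions already anticipate that adding psychosocial measures will improve accuracy. Recruitment alone could produce a result that seems to confirm this.

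**Working it through.** **Plan's own figure.** The protocol gives no figure for the exploratory aim. Its one precision figure, a half-width of 0.10 at AUC 0.70, serves as a yardstick. I used the Hanley-McNeil standard error with site counts divided by the design effect 1 + 4 × 0.5 = 3. The half-width is 0.086 if 36% prevalence holds in all 100 participants, 0.106 at 36/10/0% and 0.112 if only heel-pain participants have trigger points. The stated 0.10 lies in this range.

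**Inputs from the protocol.** Groups of 50, 25 and 25 with five muscles each give 250, 125 and 125 sites. Prevalence is 36% in plantar heel pain.

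**Assumptions (not in the protocol).** Prevalence is 10-20% in Achilles sites and 0-10% in pain-free sites. The score is normal with SD 1, is higher by d = 1 or 1.5 in both pain groups alike, and has no link to trigger points within any group.

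**Formula.** Let π+ and π− be the shares of positive and negative sites that belong to people with foot pain. Then

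AUC = 0.5 + [Φ(d/√2) − 0.5] × (π+ − π−)

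with Φ(1/√2) = 0.760 and Φ(1.5/√2) = 0.856.

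Example, 36/10/0%: the positives are 90 + 12.5 + 0 = 102.5, all in people with pain, so π+ = 1. The negatives are 160 + 112.5 + 125 = 397.5, so π− = 272.5/397.5 = 0.686. For d = 1, AUC = 0.5 + 0.260 × 0.314 = 0.582.

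| Achilles / control prevalence | π+ | π− | AUC, d = 1 | AUC, d = 1.5 |
|---|---|---|---|---|
| 10% / 0% | 1.000 | 0.686 | 0.582 | 0.612 |
| 20% / 0% | 1.000 | 0.675 | 0.584 | 0.615 |
| 10% / 10% | 0.891 | 0.708 | 0.548 | 0.565 |
| 20% / 10% | 0.902 | 0.698 | 0.553 | 0.573 |
| 36% / 36% | 0.750 | 0.750 | 0.500 | 0.500 |
| 10% / 36% | 0.695 | 0.773 | 0.480 | 0.472 |

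**Where it vanishes or reverses.** The sign is that of π+ − π−, so the turning point is a control prevalence equal to the pooled prevalence of the two pain groups. That is (90 + 12.5)/375 = 27.3% with Achilles at 10%, and (90 + 25)/375 = 30.7% with Achilles at 20%. Above it the score's AUC falls below 0.50.

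**Restriction to the 75.** Without the controls π+ = π− = 1, so the AUC is 0.50 for any d.

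**Gain over imaging.** I simulated 400,000 observations in the 50/25/25 mix. The imaging marker was raised by √2 × Φ⁻¹(0.70) = 0.74 SD in trigger-point tissue, and a logistic model was fitted with and without the score. Over the first four rows of the table the gain was +0.005 to +0.015 for d = 1 and +0.009 to +0.029 for d = 1.5. The score's standardised weight was between about a fifth and just over a half of the imaging marker's weight.

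**Scale.** The sample size section assumes imaging AUCs uniform from 0.5 to 0.8. A spurious 0.548-0.584 would exceed 0.048/0.30 = 16% to 0.084/0.30 = 28% of those candidates on univariate AUC.

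**The case against.** The strongest reply is that size and direction both rest on prevalences the protocol does not give. A trigger point is defined as a tender taut band, without requiring reproduced heel pain, so pain-free controls can be positive. The 36% refers to active points only. This stands: the artefact is possible, not built in. Even on favourable assumptions the spurious gain is small against a planned half-width of 0.10, and the aim is exploratory. That limits the weight of the point. It does not rescue the reading as relative contributions, since bias does not shrink with precision and the anticipated conclusion points the same way.

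Three of the six psychological scores are not described as pain-referenced. That stands too, although any score that runs higher in people with pain behaves the same way.

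A restricted run might also be planned in a fuller document. The article nevertheless states the interpretation itself, not merely the method.

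Two stronger readings are tempting, and the text supports neither.

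- A reader might infer that age, sex and BMI have been matched away and cannot be assessed. Recruitment balances groups, not trigger-point status, and positive and negative sites coexist within the heel-pain group. In a simulation with identical age distributions (assumed prevalences 36/10/10%, participant random-effect SD 1.5), age still reached an AUC of 0.60 and 0.68 for within-group log odds ratios of 0.5 and 1.0 per SD. Balancing suppresses only the between-group part. The article also does not list which demographics enter the models.
- A reader might take group membership as the outcome, as the stated objective suggests. A 1 SD score would then separate heel pain from pain-free with AUC 0.76. The exploratory models refer back to the tissue-level outcome, where the effect is much smaller.

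**Conclusion.** The point holds as a conditional one. Importance and AUC gain over all 100 participants depend on the recruited mix and cannot, without a caveat, be read as the contribution of psychological factors to identifying myofascial pain. If trigger points are clearly rarer in controls (0-10%, against 36% in heel pain and 10-20% in Achilles), a score unrelated to trigger points within any group reaches AUC 0.55-0.58 at a 1 SD shift and 0.57-0.62 at 1.5 SD. It adds +0.005 to +0.03 to a marker of AUC 0.70. At equal prevalence the effect is zero, and it reverses once controls exceed the pooled prevalence of the two pain groups.

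It would be too much to say that the ranking favours psychology by design, or that psychology would outrank imaging. For demographics, only the between-group part of importance is suppressed, which is no reason to leave them out of the ranking. This is a cheap improvement to an exploratory aim and does not touch the primary analysis.

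**What to change.** In Data Analysis, exploratory aim:

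- Estimate the importance of the psychological scores and their AUC gain over imaging also in the 75 participants with foot pain (plantar heel pain plus Achilles).
- Base any statement that psychological factors contribute to identifying myofascial pain on that result.
- Keep the all-participant result, labelled as conditional on the recruited mix.
- Note that group balancing suppresses the between-group part of the importance of age, sex and BMI, while within-group associations remain estimable. Keep them in the ranking.

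The cost is some wording and one further run on data already being collected. The restricted run is less precise, though not by much: at 36/10% its 375 sites hold 102.5 positives and 272.5 negatives, or 34.2 and 90.8 after dividing by 3. The Hanley-McNeil half-width at AUC 0.70 is then 0.109, against 0.106 for all 100 with no trigger points in controls. The restriction removes the artefact fully only if the score has the same distribution in both pain groups. A difference between heel pain and Achilles would remain, so the score means in those two groups should be shown beside the result.

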#### Sample Size

The target sample size of 50 individuals with plantar heel pain, 25 individuals with insertional Achilles tendinopathy, and 25 pain-free controls was chosen to provide a 95% CI half-width of 0.10 for an AUC of 0.70. This calculation assumes 5 muscle measurements for each participant, an intraclass correlation coefficient of 0.5 among them, and an overall active trigger point prevalence of 36% in individuals with plantar heel pain [10,74]. Further assuming that the 20 candidate biomarkers have AUCs uniformly distributed from 0.5 to 0.8, the study will have at least 85% power to obtain a biosignature meeting the desired AUC threshold.

### Alterations to Study After Initiation

To minimize missing data and maximize data quality, we have made some changes to our study protocol since study initiation. For trigger point identification, we added the step of checking to ensure that the maximum distance between the most proximal and the most distal trigger point is no more than 20 cm, to ensure that they are captured within the magnetic resonance field of view. Also, we adjusted the relative proportions of the regions of ROIs for the gastrocnemius and soleus muscles to minimize inclusion of the gastrocnemius within the soleus ROI during ultrasound imaging. For shear wave ultrasound imaging, we added the use of a gel pad over the abductor hallucis muscle to have a more equivalent imaging depth as the muscles that have a thicker superficial adipose tissue layer. For MRI, we similarly updated the slice number to routinely cover 20 cm in the calf. If global fat-water swaps are encountered, we reduce the readout matrix to 160 to reduce the first echo time, as well as reduce the phase encode number to 160 to maintain consistent voxel dimensions. We also added a B1 mapping sequence to monitor and reduce sensitivity to B1 variations [75]. ROI segmentation was updated to better accommodate oblique scan orientations and data resampling based on registration to the 3D Iterative Decomposition of water and fat with Echo Asymmetry and Least-squares estimation acquisitions. The length of the ROIs was consistent with the diameter of the fiducial markers (1.5 cm).

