#### Trigger Point Identification

Participants will lie in the prone position with knees flexed at 15° and ankles in their naturally relaxed plantarflexed posture. A physical therapist will examine 5 muscles: 3 in the calf (medial gastrocnemius, lateral gastrocnemius, and medial soleus) and 2 in the foot (abductor hallucis and flexor digitorum brevis). To facilitate consistency in the examination and imaging, the assessment will be limited to the following muscle zones, which Simons [54] has described as common trigger point locations.

Calf zones will be centered at 50% of the leg length measured from the fibular head, with the gastrocnemius zone extended proximally by 40% of the leg length, while the soleus zone will be extended distally by 30% of the leg length. For foot muscles, the abductor hallucis zone will be centered along a vertical line from the anterior medial malleolus, with medial and lateral boundaries extending 5% of the leg length [55]. The flexor digitorum brevis zone will begin 2 cm distal to the medial calcaneal tubercle and span 10% of the leg length distally. Leg length will be measured from the fibular head to the lateral malleolus. Using standardized zones based on leg length ensures that similar regions of the muscle belly are captured and helps ensure that the distance between the most proximal and distal trigger points is no greater than 20 cm, which corresponds to the MRI field of view.

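### The 20 cm limit between outermost calf marks equals the 20 cm MRI coverage and leaves no room for the 1.5 cm ROI, so marks 18.5 to 20 cm apart pass the check with outer ROIs that can be partly cut

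*Protocol article*

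**What the plan says.** Under Trigger Point Identification, the calf search zones start from the midpoint of the leg: "Calf zones will be centered at 50% of the leg length measured from the fibular head". The extents that follow are: "gastrocnemius zone extended proximally by 40% of the leg length, while the soleus zone will be extended distally by 30% of the leg length". Leg length runs from fibular head to lateral malleolus, and no value in centimetres is given. The section says that scaling the zones to leg length "helps ensure that the distance between the most proximal and distal trigger points is no greater than 20 cm", and equates that distance with the MRI field of view.

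Alterations to Study After Initiation adds three relevant facts:

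- a check that the "maximum distance between the most proximal and the most distal trigger point is no more than 20 cm", introduced so that the sites fall inside the imaged region;
- for MRI, the team "updated the slice number to routinely cover 20 cm in the calf";
- "The length of the ROIs was consistent with the diameter of the fiducial markers (1.5 cm").

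The MRI section says that ROIs are guided by fiducial markers placed over the marked sites. It also says that foot and calf are scanned with separate coils, so the 20 cm figure concerns the calf marks.

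**The concern.** The quantity analysed at each site is a measurement over an ROI that has length along the leg, not the value at a point. A separation limit equal to the coverage makes no allowance for that length. A check written to guarantee capture can then be passed by a participant whose outermost gastrocnemius and soleus ROIs are not wholly inside the slab.

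Muscle T1ρ and fat fraction are among the primary imaging outcomes, and the primary AUC pools all five muscles. A partly covered ROI still yields a mean, median and SD, but over less tissue than at other sites. Nothing in the check would flag it.

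**Working it through.** **Inputs from the protocol article**

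- Separation limit: 20 cm (Alterations to Study After Initiation)
- Calf coverage: 20 cm (same section)
- ROI length: 1.5 cm (same section)
- Gastrocnemius zone: 40% of leg length L, proximal to the midpoint (Trigger Point Identification)
- Soleus zone: 30% of L, distal to the midpoint (same section)

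**Step 1. The stated limit, with marks as points.** Slab needed = separation = 20 cm, and coverage is 20 cm. The stated figure is reproduced, with nothing to spare.

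**Step 2. The same limit, with ROIs centred on the marks.** Slab needed = separation + two half-ROIs = 20 + 2 × 0.75 = 21.5 cm. The shortfall is 21.5 − 20 = 1.5 cm. With a centred slab, each outer ROI loses 0.75 cm, and 0.75/1.5 = 50%.

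**Step 3. The limit that fits whole ROIs.** Coverage − one ROI length = 20 − 1.5 = 18.5 cm. For a separation d between 18.5 and 20 cm, the loss per outer ROI is (d − 18.5)/2: nothing at 18.5 cm, 0.375 cm (25%) at 19.25 cm and 0.75 cm (50%) at 20 cm.

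**Step 4. Whether the zones rule such separations out.** Read as one-sided extensions, the zones span 40% + 30% = 70% of L. This exceeds 18.5 cm once L > 18.5/0.70 = 26.4 cm, and 20 cm once L > 20/0.70 = 28.6 cm. For assumed L of 32, 36 and 40 cm, the span is 22.4, 25.2 and 28.0 cm.

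**Step 5. How often, for scale only.** In a simulation, two gastrocnemius marks and one soleus mark were placed uniformly in their zones (400,000 draws per leg length). Leg length and uniform placement are both assumptions.

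| Assumed L (cm) | Passes check, d 18.5–20 cm | As share of those passing | Mean loss per outer ROI in that band | Fails check, d > 20 cm |
|---|---|---|---|---|
| 28 | 1.2% | 1.2% | 12% | 0% |
| 30 | 4.5% | 4.6% | 22% | 0.9% |
| 32 | 6.8% | 7.1% | 23% | 4.4% |
| 36 | 9.2% | 10.8% | 24% | 15.3% |
| 40 | 10.0% | 13.9% | 25% | 27.9% |

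At an assumed L of 26 cm, no participant is affected.

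**The case against.** The strongest reply is that the authors foresaw the problem. They say only that the zones help to keep the distance within 20 cm, and they added an explicit check for the remaining cases. A 70% span that can exceed 20 cm is then the reason for the check and not a contradiction of it. This stands as far as it goes: the zone text promises no guarantee. It does not rescue the check, whose limit leaves no room for the ROI.

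The geometry is also partly assumed. The article does not say how the distance is measured. If it is taken mark to mark, a sideways offset makes the distance along the slab shorter. On a flat plane, the offset needed to bring 20 cm down to 18.5 cm is √(20² − 18.5²) = 7.6 cm, and smaller offsets reduce the cut without removing it. The scan parameters are in supplementary tables that are not shown, so actual coverage may differ from the routine 20 cm. The wording about centring the zones at the midpoint is ambiguous too. If the zones were truly centred there, with total lengths of 40% and 30%, they would together span only 40% of leg length, which passes 18.5 cm only above 18.5/0.40 = 46.25 cm. The one-sided reading fits the words on proximal and distal extension better, but the text should settle it.

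A reader might infer three stronger things that the document does not support:

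- **Outer sites are cut as a rule.** They are not. Up to 18.5 cm nothing is cut, and above 20 cm the check applies.
- **A participant who fails the check must have a mark moved.** The article states no action on failure, and a condensed article may leave that to the full protocol.
- **Affected sites would differ by sex.** This would need leg lengths by sex, which are not given.

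**Conclusion.** The point holds in a limited form. As written, the check does not by itself ensure that whole ROIs are imaged, because the limit equals the coverage. The exposed participants are those with outermost calf marks between 18.5 and 20 cm apart. With a centred slab, the loss is at most half of each outer ROI.

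The 1.5 cm shortfall uses only the article's own figures, given ROIs centred on the marks, distance along the slab axis and coverage of exactly 20 cm. The frequency of about 7% to 10% rests further on assumed leg lengths of 32 to 40 cm, uniform placement and the one-sided reading of the zones, so it should be read as an order of magnitude. The likely effect on the analysis is partial ROI coverage at some outer calf sites, not loss of those sites.

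**What to change.** 1. State that the distance is measured centre to centre along the slab axis. Then either set the limit to at most 18.5 cm (coverage minus one ROI length), or keep 20 cm and set calf coverage to at least 21.5 cm.
2. Under Trigger Point Identification, say whether the zones extend one way from the midpoint or are centred on it. Reconcile the sentence that they help to keep marks within 20 cm with the resulting span (70% of leg length if one-sided).
3. Among participants already scanned, flag those with marks more than 18.5 cm apart, identify any partly covered ROIs, and examine them in a sensitivity analysis of the MRI biomarkers.

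The cost is small. Under the tighter limit, more participants fail the check: in the simulation the share rises from about 4% to 11% at an assumed 32 cm, from 15% to 25% at 36 cm and from 28% to 38% at 40 cm. Extending coverage avoids this at the price of a few more slices (1.5 cm on 20 cm, or 7.5%). With 55 of 100 participants enrolled by November 2025 and enrolment open until July 2026 at the latest, the change can still protect later scans.
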